### Design

The study uses a cluster-randomized, stepped-wedge controlled trial design. Randomization will occur at the commune level and communes will be assigned to receive either the SSM intervention first or the control condition first. The control condition will be enhanced treatment as usual. Those communes assigned to receive the control condition first will receive the SSM intervention 4 months later. This will ensure that the study is conducted ethically and will not deny evidence-based services to members of the control group. Participants in the intervention and control groups will be from different communes, or municipal districts, meaning that they do not access the same service units. This will minimize the risk of contamination. Figure 2 shows how the design will operate. The *black rows* depict the experimental data collection periods, *diagonally striped rows* are the control data collection periods, and the *gray rows* represent the long-term data collection period. The primary measure of interest is the proportion of individuals in the experimental versus the control group (*black* versus *diagonal striped*) that went from being a case of depression (SRQ-20 > 7) to being non-case (SRQ-20 < 8) over the experimental data collection period. Based on the feasibility case rate of a mean of one case every 14 days, each commune is expected to have eight completed cases (baseline, month-1 and month-2 measures) per year for a total *n* of 256 cases. Figure 3 shows a SPIRIT figure depicting the study design. Additional file 1 provides an overview of the elements of the study protocol, as described in a SPIRIT checklist.  Recruitment will continue until the desired sample size is reached and data can be analyzed to assess the effectiveness of the intervention.

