### Power calculation

The number of subjects required for this randomized cluster trial was calculated by estimating the number that would be required in a completely randomized design and then adjusting this number by the design factor associated with a randomized cluster trial (Table 2). The number of subjects required for a completely randomized design was calculated by the R function pwr.t.test [29] using the following characteristics:An effect size of 0.5 (where a small effect size is 0.2; medium is 0.5; large is 0.8)Significance level – type 1 error rate (0.05)a two-sample design

Using a medium effect size (0.5) results in an estimate of 64 subjects per arm or 128 in total at an 80% power.

**Table 2 Tab2:** Sensitivity analysis

Effect size	ICC	Number per cluster	Total *N* required
0.5	0.05	8	173
0.8	0.05	8	69
0.2	0.05	8	1063
0.3	0.05	8	474
0.4	0.05	8	268
0.45	0.05	8	212
0.5	0.025	8	150
0.5	0.01	8	132
0.5	0.005	8	132
0.45	0.005	8	163

*ICC* intracluster correlation coefficient

The Design Effect (DE) is estimated by the formula:$$ D E = 1 + \left(\mathrm{n} - 1\right) \times \mathrm{p} $$where

*DE* = Design Effect

*n* = number of subjects in each cluster

*p* = ICC (intracluster correlation coefficient)

No estimates of the SRQ-20 intracluster correlation coefficient (ICC) are available; however, within the research literature on estimating sample sizes, the ICC is usually described as small with values of 0.01 to 0.05 – with a median of around 0.01. We have used the upper value of 0.05. This is the number of participants who will be found to have an SRQ-20 > 7 and will be followed up over the 2 months. This was estimated from the feasibility data, which produced approximately one subject every 14 days within primary care centres (or one every 2 weeks). We therefore estimate a mean of eight subjects per commune would be completed in the experimental or control time period, meaning that the total *n* during the study period is 32 clusters × 8 completed subjects per cluster or 256 subjects. The DE associated with eight subjects per cluster, a medium effect size of 0.05, and an ICC of 0.05 is 1.35, meaning that the randomized cluster study requires 128 × 1.35 or 173 subjects which is below the anticipated *n* of 256.

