There are three outcome variables being collected from each client in the study: SRQ-20, WHODAS 2.0 and CAGE. The SRQ-20 can be used as individual scores as well as primary of reporting the clients with scores either >7 or <8 to compute a rate for non-case as a proportion, and can be used as the entire interval of scores that are ordinal and so allow for ordinal statistics to be described as well as modeled. The WHODAS 2.0 and CAGE will be analyzed in the form they are scored, with no collapsing to subcategories unless later modeling justifies this. The SAP will describe what might be done in various circumstances.

Since the design of this study is a clustered stepped-wedge design, the descriptive statistics will be displayed in the order of the commune implementation in the wedging: first or second; 3-month intervals over the study; time of observation: baseline, month 1 and month 2, and combining the commune data to up to the district, combining districts up to provinces and finally combining the provinces to the entire country of Vietnam (see Fig. 2). These descriptive statistics will include those listed above: sample size, minimum, median, maximum, lower and upper quartiles, mean, standard deviation and interquartile range, with plots (raw distributions as well as box plots) of the variables by what will be considered as factors: commune, district, province, country, order of implementation and timing of the measurements within each commune. Patterns will be noted to be justified with the statistical analyses conducted later. One type of pattern from the descriptive statistics is to do LOESS smoothing to suggest patterns versus time and the timing may suggest some relationships with time, such as skill of staff within commune or order during the entire trial, that need to be considered in the modeling, as these could impact the assumptions of the stepped-wedge analysis.

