Overall, the primary analysis will consider the proportions of non-caseness with the SRQ-20 within commune as the response variable using logistic regression assuming a binomial response distribution as part of the glm (generalized linear model) command in R [32]. The independent variables will be the cluster (commune), order of administration, and baseline value of the response variable, and then timing of the response at months 1 and 2. If the assumptions of the binomial data are not met, then a Poisson or negative-binomial model will be considered next, as they are known to model data better than the binomial. Standard assumptions, such as residual plotting, distributions of the residuals, influence and variance inflation, are checked to see how the models are impacted with the observations for possible deletion and remodeling. Differences between the models will be detected using AIC (Akaike Information Criterion), with smaller values detecting the better models. If some models are very close to each other, these will also be reported. Models that include higher levels of the combined communes as districts, provinces and the entire country will also be explored to gain further insight as the meaning the results. Finally, the raw scores from the SRQ-20 within commune will also be modeled, but differences between this model and the proportions model will defer to the proportions model as it was prespecified as the primary outcome variable in this protocol. In the design, we did not have a study-specific measure of the IC (intraclass correlation), we will estimate it for the four ways of doing the analysis so that future studies can use these estimates in their planning. Results will reported with *p* values in comparison with an alpha value of 0.05, and no correction for multiplicity. In addition, 95% CIs (confidence intervals) will be displayed for the results to make it easier for readers to decide whether the results are clinically important as well as their statistical significance with *p* values. Similar models and methodology will be used with WHODAS 2.0 and CAGE outcome variables. Reports will include all these analyses and any deviations will follow the SAP process for reporting. It is also possible to report all proportions as percentages for a suitable audience to understand.

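### The outcome that decides the trial is SRQ-20 cut at 7/8, but the sample size was computed for a comparison of mean scores, so the stated power of about 80% at d = 0.4 does not describe the primary analysis

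*Protocol article*

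**What the plan says.** The Design section defines the primary measure as the proportion, in each group, that "went from being a case of depression (SRQ-20 > 7) to being non-case (SRQ-20 < 8) over the experimental data collection period". The Analysis section repeats this choice: "the primary analysis will consider the proportions of non-caseness with the SRQ-20 within commune as the response variable using logistic regression". The same section acknowledges that the SRQ-20 "can be used as the entire interval of scores that are ordinal and so allow for ordinal statistics to be described as well as modeled", and plans a raw-score model as well. If the two models differ, "differences between this model and the proportions model will defer to the proportions model as it was prespecified as the primary outcome variable". WHODAS 2.0 and CAGE are to be analysed as scored, without collapsing unless later modelling justifies it.

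The Power calculation section works on another scale. "The number of subjects required for a completely randomized design was calculated by the R function pwr.t.test", and "Using a medium effect size (0.5) results in an estimate of 64 subjects per arm or 128 in total at an 80% power". It ends by claiming roughly 80% power at a minimum effect size of 0.4, with eight patients per cluster and an ICC of at most 0.05.

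The inclusion criteria admit only people with SRQ-20 above 7. The primary model lists the baseline value of the response variable among its covariates.

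**The concern.** A t-test calculation gives the power for comparing mean scores. The analysis that decides the trial compares proportions either side of a cut, which uses less of the information in each score. Unless the effect is large, its power is lower than the figure quoted, and the article gives no power for the proportion.

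The baseline adjustment is affected too. Everyone enrolled is a case, so for the binary outcome the baseline value is the same for every participant and the covariate, as written, does nothing. The raw-score model has real variation to use: pilot baseline scores ran from 8 to 17.

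At stake is whether a benefit of the size the sponsor plans for would be detected by the primary test.

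**Working it through.** **Inputs from the article.** 32 communes × 8 = 256 participants; ICC 0.05; alpha 0.05; d = 0.5, minimum 0.4. Pilot follow-up: mean 4.7, with 62/71 below 8.

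**Assumptions not in the article.** Equal arms; two-sided test; near-normal 2-month scores with the same SD in both arms. The control non-case rate is not given, so two positions of the cut are used: SSM at the pilot rate of 62/71, and the cut midway between the arm means (close to the most favourable position).

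**The plan's own figures.** A t-test with d = 0.5 and 80% power needs 63.8, so 64 per arm and 128 in total. Design effect = 1 + 7 × 0.05 = 1.35, and 128 × 1.35 = 172.8, so 173. Both reproduce.

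**Score, closed form.** Effective n per arm = 256 / 1.35 / 2 = 94.8. At d = 0.4, the noncentrality is 0.4 × √(94.8/2) = 2.75 and t-test power is 78.2%. At d = 0.5 it is 3.44 and power is 92.9%. So the claim of about 80% at d = 0.4 is nearly right, but for the score.

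**Cut, closed form.** With a normal score, p_control = Φ(z(p_SSM) − d). Power = Φ{[(p_SSM − p_control)√n − 1.96√(2p̄(1 − p̄))] / √(p_SSM·q_SSM + p_control·q_control)}, with q = 1 − p.

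Example for d = 0.4 with SSM at 62/71 = 0.873: z = 1.142, so p_control = Φ(0.742) = 0.771. The numerator is 0.1023 × 9.737 − 1.96 × 0.541 = −0.064, the denominator is 0.536, and power = Φ(−0.12) = 45.3%.

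| d | Score | Cut, SSM at 62/71 (control) | Cut midway (control v SSM) | Loss, points |
|---|---|---|---|---|
| 0.4 | 78.2% | 45.3% (77.1%) | 58.9% (42.1% v 57.9%) | 19 to 33 |
| 0.5 | 92.9% | 64.6% (74.0%) | 78.0% (40.1% v 59.9%) | 15 to 28 |
| 0.8 | >99.9% | 97.4% (63.4%) | 99.3% (34.5% v 65.5%) | 1 to 3 |

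**Cluster simulation.** The closed form applies the same ICC to both scales, but dichotomising also shrinks the ICC. A simulation allows for this: 16 + 16 communes of 8, ICC 0.05 on the score, integer scores 0–20, SD = (7.5 − 4.7)/1.142 = 2.45, t-test on commune means or commune proportions, 20,000 runs.

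| d | Position of cut | Score | Cut | Loss, points |
|---|---|---|---|---|
| 0.4 | SSM at 62/71 | 75.1% | 48.6% | 26.5 |
| 0.4 | midway | 75.8% | 60.9% | 14.9 |
| 0.5 | SSM at 62/71 | 91.3% | 69.2% | 22.1 |
| 0.5 | midway | 91.0% | 80.1% | 10.9 |

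Taking 87% exactly (SD 2.49) moves these figures by less than one point.

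**Size needed for 80% power on the cut, with design effect 1.35.** About 270 to 365 in total at d = 0.5 and 421 to 583 at d = 0.4, against 256 planned.

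**Baseline term.** Entry requires SRQ-20 above 7; the response is SRQ-20 below 8. At baseline the response is therefore zero for every participant in every commune.

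**The case against.** Caseness is a defensible endpoint. It mirrors the entry definition, it rests on an instrument adapted and tested in Vietnam, and a recovery rate suits a trial meant to inform policy. That a fall from 8 to 7 counts as success and a fall from 17 to 8 does not is true of any remission endpoint. Naming the SRQ-20 as the primary measure in the Outcome assessment section identifies the instrument and does not contradict the Design section. All of this stands.

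A reader might infer that the deferral rule is itself a fault, or that it would oblige the sponsor to report a null result and suppress a positive score result. The article does not support either. Letting a prespecified primary outcome prevail is sound practice, and the Analysis section promises 95% confidence intervals and a report of all these analyses.

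A reader might also take the 33-point loss as the headline. It combines the pilot's 87% with d = 0.4, which implies about 77% non-cases among controls, whom the article expects to receive little or no treatment. The article itself distrusts the pilot estimate because follow-up times varied. If SSM reached 87% and controls only 70%, 65% or 60%, the cut would have about 82%, 95% or 99% power. Those rates, however, correspond to d of about 0.60, 0.74 and 0.87, above the planning values of 0.4 to 0.5.

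If 0.4 to 0.5 meant Cohen's h on proportions, the primary analysis would keep about 78–93% power. The article names a t-test function, so that is not the documented reading.

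The baseline term may have been meant as the individual score. If so, the text should say so. How much a baseline-score covariate would gain cannot be stated, because the article gives no correlation between baseline and follow-up.

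The strongest remaining objection is to the remedy: recruitment is under way, randomisation is done and registration was retrospective, so a change of primary outcome invites criticism.

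**Conclusion.** The concern holds in a limited form. The trial is sized for a comparison of means and decided on a proportion, and the stated power of about 80% at d = 0.4 belongs to the first. For the proportion, power is about 45–61% at d = 0.4 and 65–80% at d = 0.5, against 75–78% and 91–93% for the score. The simulated loss of 11 to 27 points is the better guide, because it allows for the smaller ICC of the cut outcome. At d = 0.8, the size category in which the article places the pilot, the loss nearly vanishes.

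The direction is secure; the size depends on near-normal scores and on an unstated control rate. Both calculations compare two groups at 2 months, and neither is the planned logistic model with months 1 and 2. The constant baseline term follows from the entry criterion alone, provided the response is read as the article defines it.

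**What to change.** Preferred: by a dated, disclosed amendment made before any comparative data are seen, make the 2-month SRQ-20 score model primary, with an SSM/control term, the individual baseline SRQ-20 score as covariate and commune as a random effect. This matches the basis of the sample size. Keep the proportion with SRQ-20 below 8, with its 95% confidence interval, as the first secondary outcome, and reword the deferral sentence to match.

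If the sponsor prefers caseness as primary: keep the deferral rule, adjust the logistic model for the individual baseline SRQ-20 score, and restate the power for the proportion over a stated range of control rates. The article already allows longer recruitment and additional communes to reach its target, should that target rise.

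Cost: protocol, registry and SAP wording (the article says the SAP follows submission; it may now exist). No new visits or measurements are needed for the preferred route, since the score model is already planned. The real price is a disclosed change of primary outcome after recruitment began, in a retrospectively registered trial, and a headline mean difference that is less immediate than a recovery rate. The alternative avoids that price but may need more participants.

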### Data management

Hard copy versions of the questionnaires will be completed by the health and social workers at baseline. Each CHS has a trained health worker who will be responsible for inputting the data into an electronic format using EpiData software [36]. The electronic version will be saved on a secure server. The hard copy questionnaires will be stored in a locked cabinet at the CHS. One- and 2-month assessments will be collected by telephone by outcome assessors based in Hanoi. Data will be similarly entered using EpiData software. Only authorized research team members have will access to hard copy and electronic questionnaires. The hard copy questionnaires and the electronic versions will be saved for 5 years and will then be destroyed, according to Vietnamese requirements. All prescreening data for families that are not recruited to the study will be stored in a locked cabinet in the CHS, and will be destroyed after 1 year, as is standard practice in Vietnam.

### Data monitoring

The Data Monitoring Committee (DMC) will be composed of [name] from Simon Fraser University in Vancouver, a representative from the Institute of Population, Health and Development (PHAD) who is not otherwise involved in the study, and a representative from the Hanoi School of Public Health who is also not involved in the study. The DMC’s mandate will align with the description found in the SPIRIT guidelines [37]. The committee will meet once annually for the duration of project, and will report any concerns to the principal investigators of the study. The DMC is independent from the study sponsor and has no competing interests.

Any important modification to the protocol will be reported by the principal investigators and study team to the research coordinator (JM), who will then communicate them to research ethics boards, the study sponsor, the trial registry and relevant journals.

### Ancillary and post-trial care

While the risks associated with SSM are minimal, it is possible that study participants may experience no improvement in depression symptoms as a result of the intervention, and that they will have a relapse of symptoms post trial, or that they may experience other unexpected outcomes. The involvement of social workers and primary care providers in this study will help to mitigate the risks associated with these circumstances, as the relationship between social workers and patients will not end at the end of the trial period. Social workers will remain in place in the community, and will continue to act as a support to patients and as a bridge between patients and other services. Similarly, this study will increase awareness among community members about the availability of supports for depression in primary care. Patients may continue to access these services after the trial has ended.

## Discussion

This trial plans to assess the effectiveness of a low-cost, community-based intervention for adult depression in eight provinces of Vietnam. Services for depression are very limited in the country, and are currently almost completely unavailable in the primary care context. This trial should provide important evidence about the effectiveness of a SSM intervention that has been validated for use in the Vietnamese context, helping to inform the scale-up of community-based depression services in the country.

This trial takes place in the context of a favorable policy environment, as the government of Vietnam is committed to enhancing community-based services for mental illness, including depression. This study is conducted in partnership with the Vietnamese Ministry of Labor, Invalids and Social Affairs (MOLISA) and with the cooperation of the Ministry of Health. The partnership with the government of Vietnam, and the alignment of this trial with the policy priority to improve community-based mental health services, has several advantages. This trial should produce rigorous data about the effectiveness of the intervention which will be disseminated directly to the ministries and departments of health and social services. This integrated knowledge translation approach hopes to promote evidence-based policy and service development. The involvement of the Government of Vietnam should also help to foster the sustainability and further scale-up of the intervention should the findings be positive. This trial, therefore, has the potential to lead to lasting improvement in access and availability of depression services in Vietnamese communities.

One study limitation is that the trial takes place in eight of Vietnam’s 63 provinces and, therefore, might not be representative of the diversity of the Vietnamese population. Vietnam is home to 54 ethnic groups [38] and there is variation in culture and language between the northern, central and southern regions of the country. Because this trial takes place in provinces in all three regions of the country, however, we are confident that the results could be generalizable.

An additional limitation is that the study measures and tools were designed in Western countries and may, therefore, not be culturally valid for use in Vietnam. We are confident, however, that the work we conducted during the feasibility study, including a review of depression measures that have been validated for use in Vietnam and among Vietnamese populations [25] and the validation of the *Antidepressant Skills Workbook*, support the appropriateness and validity of these measure and tools for use in Vietnam. While the CAGE was not used during the feasibility study, it has been validated for use in many countries, including low-income settings [39] and has been used by Tran et al. [40] in a study of the interaction of perinatal common mental disorders, alcohol use and domestic violence in Vietnam.

## Trial status

At the time of submission, the MAC-FI trial is ongoing, with patient recruitment currently underway.

## Abbreviations

AIC: Akaike Information Criterion
ANOVA: Analysis of variance
CAGE: Cut-down, Annoyed, Guilty, Eye-opener
CHS: Commune Health Station
CI: Confidence intervals
DALYs: Disability-adjusted Life Years
DE: Design Effect
DMC: Data Monitoring Committee
DOLISA: Department of Labor, Invalids and Social Affairs
glm: Generalized linear model
IC: Intraclass correlation
ICC: Intracluster correlation coefficient
ITT: Intention-to-treat
LMIC: Low- and Middle-income country
MOLISA: Ministry of Labor, Invalids and Social Affairs
PHAD: Institute of Population, Health and Development
RCT: Randomized controlled trial
SAP: Statistical Analysis Plan
SRQ: Self-reporting Questionnaire
SSM: Supported Self-management
WHODAS: World Health Organization’s Disability Assessment Scale
